### 2.4. Timeline

After enrollment in the BRIDGE cohort, patients will remain in the study until loss to follow-up or completion of the 90-day assessment post-onset. Data will be collected at four time points: (1) enrollment, (2) day 7 of hospitalization, (3) hospital discharge, and (4) 90 days after stroke onset (Figure 1).

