### 2.12. Data Management and Follow-Up

Patient data will be managed in compliance with Japanese data protection guidelines. A unique study number will be assigned upon enrollment. Follow-up assessments will be conducted via telephone at 90 days post-onset, collecting data on survival, employment, and mRS. If unreachable after multiple attempts, patients will be considered lost to follow-up. Informed consent includes potential secondary use of anonymized data, contingent on new ethical approval.

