### 2.14. Statistical Methods

There is no maximum sample size for this study; however, the outcome may be subject to targets or maximum sample sizes, which will be specified in the relevant sub-protocol. The expected sample size is ≥200 patients (minimum 10 patients/facilities, ≥20 facilities) to provide a sufficient number of different rehabilitation doses to predict functional outcomes and build robust models for protocol use. To avoid over-representation of some centers, data collection is limited to 50 patients per facility. Patient enrollment will therefore not be strictly equal across hospitals; each facility is expected to enroll at least 10 patients, with a maximum of 50 patients, depending on their clinical volume. This strategy ensures diversity in practice patterns while preventing over-representation of any single center. The number of enrolled patients and facilities is a sufficient sample size to capture the various variations in practice and treatment. It is considered feasible to collect a sample of this calculated size because each participating facility should be able to enroll at least one patient per month based on the number of stroke patients hospitalized at each facility in the past.

Baseline characteristics and outcomes will be summarized using descriptive statistics. Continuous variables will be presented as means with standard deviations (SDs) or medians with interquartile ranges (IQRs), while categorical variables will be presented as frequencies and percentages (*n*, %).

The primary analysis will examine the association between the mean rehabilitation dose (MQS score) during the first 7 days of hospitalization and the primary outcome of a favorable functional outcome (mRS ≤ 2) at 90 days. This association will be evaluated using a multivariable logistic regression model. The model will be adjusted for a pre-specified set of covariates selected for their established prognostic significance, including age, sex, pre-admission mRS, baseline National Institutes of Health Stroke Scale (NIHSS) score, stroke subtype (ischemic or hemorrhagic), and participating facility (as a random effect).

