For secondary outcomes, multivariable linear regression models will be used for continuous variables, such as the Barthel Index. A pre-specified subgroup analysis will be conducted to explore whether the effect of rehabilitation dose is modified by initial stroke severity. An interaction term between the MQS score and the severity category (defined by baseline NIHSS) will be introduced into the primary model.

Time-to-event outcomes will be analyzed using Kaplan–Meier curves and Cox proportional hazards regression models, adjusted for baseline characteristics. For survival analysis, patients will be stratified into groups based on quartiles of rehabilitation volume and pre-defined stroke severity categories. Missing data for covariates will be handled using multiple imputation under the missing-at-random assumption. The primary analysis will be based on the pooled results from the imputed datasets, with a complete-case analysis performed as a sensitivity analysis.

All statistical analyses will be performed using JMP (version 13.0; SAS Institute, Cary, NC, USA) and IBM SPSS software (version 23.0; IBM, Armonk, NY, USA). A two-sided *p*-value of <0.05 will be considered statistically significant.

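### Imputation limited to covariates leaves patients unreachable at day 90 out of both the primary analysis and its sensitivity analysis, although earlier mRS and NIHSS are recorded

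*Protocol article*

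**What the plan says.** Section 2.14 fixes the scope of the imputation: "Missing data for covariates will be handled using multiple imputation under the missing-at-random assumption". It continues: "The primary analysis will be based on the pooled results from the imputed datasets, with a complete-case analysis performed as a sensitivity analysis". The endpoint in the primary model is "the primary outcome of a favorable functional outcome (mRS ≤ 2) at 90 days", and on the method it says "This association will be evaluated using a multivariable logistic regression model". The adjustment set is age, sex, pre-admission mRS, baseline NIHSS, stroke subtype and a random effect for facility. Nothing measured after baseline is in it except the exposure, the mean MQS over days 1–7.

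Section 2.12 obtains the 90-day mRS by telephone and adds: "If unreachable after multiple attempts, patients will be considered lost to follow-up". No section says how such a patient enters the analysis.

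Earlier outcome information is planned. Section 2.4 states: "Data will be collected at four time points: (1) enrollment, (2) day 7 of hospitalization, (3) hospital discharge, and (4) 90 days after stroke onset". Table 1 schedules the mRS at all four times, and section 2.8 records the NIHSS at admission, day 7 and discharge. None of the post-baseline values has a stated role when the 90-day mRS is missing. Section 2.6 counts death as mRS 6, and Table 2 has the date of death recorded.

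**The concern.** A logistic model for a single 90-day outcome cannot use a record without that outcome. Imputing covariates alone does not change this. The primary analysis and the complete-case analysis would therefore differ only in patients with missing covariates. Agreement between them would say nothing about loss at day 90.

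Loss related to recovery is plausible. Section 2.13 has patients going on to post-acute facilities or community care according to their condition and regional resources, so how easily they are reached by telephone may depend on their state at discharge. Discharge status lies between the exposure and the outcome and is rightly absent from the analysis model, so that model cannot account for such loss. An imputation model can use it without adjusting the dose effect for it.

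**Working it through.** **1. Who drops out**

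| Patient at day 90 | Primary analysis (covariates imputed) | Complete-case analysis |
|---|---|---|
| mRS known, covariates complete | in | in |
| mRS known, a covariate missing | in | out |
| Known death (mRS 6) | in, not favourable | in, if covariates complete |
| Unreachable, status unknown | out | out |

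The last row is the problem.

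**2. Numbers analysed**

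The expected sample size in section 2.14 reproduces as 10 patients × 20 facilities = 200. The article names twelve hospitals elsewhere. That is a separate matter, and 200 serves here only as a reference. With loss fraction d (assumed; the article gives none), the number analysed is 200 × (1 − d). The enrolment needed to keep 200 is 200 / (1 − d), rounded up. The standard error grows roughly by 1/√(1 − d).

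| d | Analysed | Enrolment to keep 200 | SE factor |
|---|---|---|---|
| 5% | 190 | 211 | 1.03 |
| 10% | 180 | 223 | 1.05 |
| 15% | 170 | 236 | 1.08 |
| 20% | 160 | 250 | 1.12 |

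**3. Precision that imputation can recover**

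In simulations at n = 200 (400 replicates) with 20% lost depending on discharge status only, the SE of the log odds ratio per SD of dose was 0.165 with no loss, 0.187 with lost patients dropped, and 0.180 with the outcome imputed from discharge status. The rough rule agrees: 0.165/√0.8 = 0.184. The gain is (0.187 − 0.180)/0.187 = 3.7%, about 4%. Bias in that setting was negligible.

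**4. Bias**

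One large simulated sample (n = 400,000), all parameters assumed:
- Severity S is standard normal. Dose Q = −0.5·S + 0.87·noise.
- Discharge disability D = 0.8·S − 0.35·Q + noise.
- Logit of a favourable outcome = 0.1 − 1.5·D.
- The analysis model is the outcome on Q and S. With no loss, the odds ratio for Q is 1.46.
- Loss is logistic in the terms shown, with the intercept set to give 10% or 20% lost.
- The comparator imputes the missing outcome once, stochastically, from Q, S and D.

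| Loss depends on | Lost dropped, 10% | Lost dropped, 20% | Outcome imputed |
|---|---|---|---|
| Nothing | 1.46 | 1.47 | 1.46–1.47 |
| Severity and dose (0.8·S − 0.5·Q) | 1.46 | 1.47 | 1.46–1.47 |
| Discharge status (D) | 1.44 | 1.41 | 1.46 |
| Poor status, more so at low dose (D − 0.5·Q − 0.6·Q·D) | 1.34 | 1.25 | 1.46–1.47 |
| Good status, more so at low dose (−D + 0.6·Q·D) | 1.54 | 1.59 | 1.46–1.47 |

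On the log scale at 20% loss, the shifts are ln(1.41/1.46) = −0.03, ln(1.25/1.46) = −0.16 and ln(1.59/1.46) = +0.09. Against the SE of 0.187 from step 3, these are about 0.2, 0.8 and 0.5 standard errors.

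A separate simulation (n = 4,000, 60 replicates) with 7.5% lost, depending on discharge status and dose, moved the log odds ratio from 0.45 to 0.50. Imputation from discharge status returned 0.45.

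The imputed column is a favourable case. Loss was generated from variables in the imputation model, and D was a single continuous auxiliary.

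**The case against.** The strongest reply is that the article never says these patients are excluded. It describes covariates, is silent on the outcome, and condenses a fuller plan that may cover the rest. A reader might infer a written exclusion rule, and there is none: exclusion follows from covariate-only imputation combined with a single-time-point logistic model. The reply does not dispose of the point. The article does set the imputation scope, the basis of the primary analysis and the sensitivity analysis, and a plan that followed this text would carry the gap forward.

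A reader might also infer that the primary odds ratio will be biased. The documents do not support that. Dose, baseline severity, age, pre-admission mRS and facility are in the model, and loss driven by dose and baseline severity caused no material bias above. Loss that followed discharge status alone caused little. The larger shifts need a joint dependence on discharge status and dose that nothing in the article establishes, and their sign depends on who is lost.

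Two further readings go too far. Deaths are not lost outcomes when they are known. Nor can one say that most missing data will arise at day 90: section 2.12 allows several contact attempts, and no missingness rate is given for any variable.

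Finally, a large imputation model could be unstable in about 200 patients with as few as 10 per facility. That stands, and it limits the fix.

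**Conclusion.** The point holds as a weakness in a stated rule. Under the text as written, patients unreachable at day 90 with unknown status would in effect be absent from the primary analysis and from the one sensitivity analysis. The certain cost is precision, and imputation recovers only a little of it (about 4% of the SE in the 20% scenario). The possible cost is bias of unknown size and direction, which the planned sensitivity analysis could not show. Under assumed loss of 7.5–20% it ran from negligible to material, and was material only where loss depended on discharge status and dose together. The loss rates and all simulation parameters are assumptions. The case for change rests on how cheap the protection is, not on a demonstrated bias. It is a sensible improvement, not a fatal flaw.

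**What to change.** Amend the missing-data sentences in section 2.14 along these lines:

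- Multiple imputation covers missing covariates and a missing 90-day mRS; known deaths are set to 6 before imputation.
- The imputation model contains MQS, the covariates of the primary model, facility, and a small set of auxiliaries already collected, for example discharge mRS and either discharge or day-7 NIHSS. The auxiliaries stay out of the analysis model because they follow or overlap the exposure.
- Sensitivity analyses: (a) patients with an observed 90-day mRS only; (b) a delta-shifted version in which imputed outcomes are made worse, and then better, than missing-at-random implies, over a range fixed in advance.

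No new data are needed. The cost is a few sentences, a little more analysis work, and the discipline of keeping the imputation model small at about 200 patients. Section 2.1 puts the start of enrolment in June 2026, so the change can be fixed before any outcome is seen.

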## 3. Discussion

This multicenter prospective cohort study aims to evaluate the association between rehabilitation dose quantified using MQS and functional outcomes in patients with acute stroke. The study is designed to address the current lack of evidence regarding optimal early mobilization parameters, particularly in the acute phase of stroke care. While early rehabilitation has been widely promoted in recent years, clinical practices remain variable, with no established consensus on ideal dose, timing, or intensity [34]. Our study is the first large-scale investigation in Japan to quantitatively assess daily rehabilitation dose using a validated measure and its relationship with long-term independence in activities of daily living.

Prior studies on early mobilization in stroke patients have yielded inconsistent findings. For instance, while very early mobilization was associated with poorer outcomes in some randomized controlled trials [14], further post hoc analyses have suggested that mobilization delivered in shorter, more frequent sessions may improve recovery [15]. These conflicting findings may be attributed to differences in rehabilitation intensity, timing, patient severity, and methodological inconsistencies across studies [12]. By incorporating MQS, which integrates both mobilization level and duration, our study provides a more comprehensive and standardized approach to measuring rehabilitation exposure [16]. Furthermore, by stratifying patients based on stroke severity, our study will allow exploration of differential responses to rehabilitation dose, which may help define individualized, severity-specific strategies.

Another strength of this study is the integration of multiple functional, physical, and clinical outcomes, including mRS, Barthel Index, Medical Research Council score, muscle ultrasound, and frailty assessments, which enables a multifaceted evaluation of recovery. The inclusion of ultrasound to objectively assess atrophy of the rectus femoris provides novel insight into the impact of early mobilization on muscle preservation, which has been relatively underexplored in stroke rehabilitation research [35,36]. Additionally, our protocol controls for key patient-level and institutional factors, including comorbidities, nutritional status, rehabilitation policy, and institutional staffing, enhancing the robustness of our multivariate analyses.

By quantifying early rehabilitation dose with MQS over days 1–7 and linking it to 90-day outcomes, this protocol is designed to yield directly actionable outputs for practice. First, clinicians can translate MQS into severity-specific dose targets during daily rounds, facilitating individualized prescriptions rather than one-size-fits-all approaches. Second, routine rectus femoris ultrasound enables early detection of muscle atrophy and dose adjustment when deterioration is observed. Third, aggregating MQS and outcomes at the facility level provides benchmarking metrics that support quality-improvement cycles and alignment across centers. Finally, these data can inform guideline refinement and the design of future randomized trials by identifying dose bands and patient subgroups most likely to benefit.

Nevertheless, some limitations must be acknowledged. First, as an observational study, causal relationships cannot be definitively established. Second, rehabilitation practices are not standardized across facilities, which may introduce variability. However, this also enhances external validity by reflecting real-world conditions. Finally, the use of telephone interviews for follow-up assessments may be susceptible to recall bias, although structured questionnaires and clear documentation (e.g., who assisted in responses) aim to minimize this limitation [37].

## 4. Conclusions

This study will be the first multicenter prospective cohort study in Japan to investigate the association between rehabilitation dose and functional outcomes in patients with acute stroke using a standardized measure, the MQS. By exploring dose–response relationships stratified by stroke severity and incorporating multiple physical and functional indicators, the study seeks to identify optimal rehabilitation strategies that are individualized, evidence-based, and implementable in real-world clinical settings. The findings of this study are expected to contribute to the standardization of early rehabilitation protocols and to improve long-term outcomes for stroke patients across diverse healthcare environments.

## Figures and Tables

**Figure 1 jcm-14-06786-f001:**
[figure not shown]
Flowchart of performed questionnaires during the study. Clinical Frailty Scale, CFS; Medical Research Council, MRC; Functional Status Score for the Intensive Care Unit, FSS-ICU.

**Table 1 jcm-14-06786-t001:** Schedule of enrolment, interventions, and assessments.

	Enrolment	Post-Allocation		Close-Out
TIMEPOINT	Hospital Admission T0	Day 7 T1	Hospital Discharge T2	After Day 90 T3
**ENROLMENT**				
Eligibility screen	×			
Informed consent	×			
Cohort enrollment (index date)	×			
**ASSESSMENTS:**				
Baseline variables	×			
Muscle cross-sectional area muscle thickness	×	×		
Physical functions (Clinical Frail Scale)	×	×	×	×
Physical functions (Functional status score-ICU, Barthel index)		×	×	
Muscle strength (Medical Research Council, Handgrip)		×	×	
mRS	×	×	×	×
Exposure ascertainment (MQS; mean of Days 1–7)		×	×	

Abbreviations: ICU; intensive care unit, mRS; modified Rankin Scale, MQS; Mobilization Quantification Score.

**Table 2 jcm-14-06786-t002:** Details of outcome measures at follow-up.

Variable	Description
Survival	If a patient dies during follow-up, date of death is recorded
Employment status	Whether the patient/family has a job at follow-up (full-time or part-time) and whether the job is the same as before hospital admission
General information	Readmission to hospital during follow-up
National Institutes of Health Stroke Scale	The National Institutes of Health Stroke Scale is a 15-item impairment scale, intended to evaluate neurologic outcome and degree of recovery for patients with stroke. The scale assesses level of consciousness, extraocular movements, visual fields, facial muscle function, extremity strength, sensory function, coordination, language, speech, and hemi-inattention.
Physical function/activities of daily living	
mRS	The mRS ranges from 0 (no symptoms) to 6 (death) and is the most widely used functional outcome measure in stroke trials. An mRS ≤ 2 at 90 days is defined as a favorable outcome.
Clinical Frail Scale	The Clinical Frailty Scale is a judgment-based frailty tool that evaluates specific domains, including comorbidity, function, and cognition, to generate a frailty score ranging from 1 (very fit) to 9 (terminally ill).
FSS-ICU	The FSS-ICU is a performance-based measure that assesses physical function in critically ill patients. It evaluates five tasks: (1) rolling, (2) supine to sit transfer, (3) sitting at the edge of the bed, (4) sit to stand transfer, and (5) walking. Each task is scored from 0 (unable to perform) to 7 (complete independence), for a total score ranging from 0 to 35. Higher scores indicate better physical function.
MRC score	The MRC score is a bedside tool used to assess muscle strength in critically ill patients. It evaluates six muscle groups bilaterally: shoulder abduction, elbow flexion, wrist extension, hip flexion, knee extension, and ankle dorsiflexion. Each muscle group is graded on a scale from 0 (no contraction) to 5 (normal strength), yielding a total score ranging from 0 to 60. A score below 48 typically indicates clinically significant muscle weakness.

mRS; modified Rankin Scale, MRC score; Medical Research Council score, Functional Status Score for the ICU; FSS-ICU, MUST; Malnutrition Universal Screening Tool.

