## 1. Introduction

Stroke is a leading cause of disability worldwide [1] and ranks fourth among the top ten causes of death in Japan. Although advances in medical science have improved survival rates for patients with severe stroke in recent years, the number of individuals living with long-term physical and cognitive sequelae has increased [2,3]. Among these, muscle atrophy in the paralyzed limbs of patients with hemiplegia, referred to as central atrophy, significantly affects both functional independence and quality of life [4]. In addition to stroke-related disability, critically ill patients may experience other complications, such as intensive care unit (ICU) acquired weakness, characterized by generalized weakness of the limbs and respiratory muscles, further impeding recovery [5,6]. Skeletal muscle atrophy in severely ill patients progresses rapidly by approximately 2% per day, amounting to a 12% reduction in muscle mass per week, and is directly associated with loss of functional independence and reduced quality of life. Therefore, early detection and prevention of muscle atrophy are crucial [7].

Rehabilitation is a primary strategy to promote functional recovery and enhance independence in stroke patients [8]. Once the patient’s neurological symptoms and vital signs stabilize during the acute phase, those with functional impairments transition to the post-acute phase and begin rehabilitation. Traditionally, active rehabilitation has been implemented during the post-acute phase, when patients are medically stable, with the goal of minimizing long-term disability [9]. More recently, increasing attention has been paid to early mobilization in critically ill patients. While several studies have reported the safety of early mobilization, its effectiveness remains a subject of debate [10]. Several systematic reviews and guideline papers have highlighted both the potential benefits and uncertainties of very early mobilization after stroke, noting variability in outcomes depending on patient severity, timing, and dose of interventions [11,12,13]. For example, one study reported that very early mobilization was associated with poorer functional outcomes and higher rates of adverse events at 3 months post-stroke compared to standard care [14]. However, a post hoc analysis of the same cohort revealed that patients who received shorter and more frequent mobilization sessions had significantly improved functional outcomes [15].

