### 2.5. Participants

a. Inclusion criteria:Patients diagnosed with acute stroke, specifically including ischemic stroke (cerebral infarction) and hemorrhagic stroke (intracerebral hemorrhage), who are expected to be hospitalized for ≥7 days. Patients with subarachnoid hemorrhage or transient ischemic attack (TIA) will be excluded because their rehabilitation course differs substantially from that of ischemic and hemorrhagic stroke;Age ≥ 18 years;Provision of informed consent;Initiation of rehabilitation by day 2 of admission.

b. Exclusion criteria:Pre-hospitalization mRS ≥ 3 (unable to walk even with aids);Terminal care patients or those with non-curative intent;Patients with anticipated prolonged immobility due to trauma (e.g., multiple unstable fractures, burns, amputations);Inability to communicate in Japanese;Explicit refusal to allow use of clinical data for research.

c. Anticipated cohort characteristics and planned reporting.

Based on stroke case-mix in the participating hospitals, we anticipate a sex distribution of approximately 55–60% male and 40–45% female, with a mean age around 70 years. For transparency and comparability, we predefine age strata as <65, 65–79, and ≥80 years. Baseline characteristics will be summarized overall and, where appropriate, by sex and age group.

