### 2.7. Secondary Outcomes

As secondary outcomes, we first selected the item of change in muscle atrophy using ultrasound examination [7,22]. This will allow us to determine the optimal MQS dose for muscle atrophy results. Next, we selected the items of the Barthel Index [26], Medical Research Council score [27], functional status score in ICU [28], grip strength [29], Clinical Frailty Scale [30], return to work, and complications. We aim to investigate these items and quantify ICU-acquired weakness from multiple perspectives (Table 2). We will also record adverse events during the rehabilitation intervention (falls, cardiac arrest, tachycardia > 130 bpm, systolic blood pressure < 80 or >200, ventricular tachycardia, other dangerous arrhythmias, arterial oxygen saturation of pulse oximetry < 80% for >3 min, and other device removal).

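### The bilateral MRC sum mixes hemiparesis with ICU-acquired weakness, so an association between MQS and MRC cannot be read as an effect on acquired weakness

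*Protocol article*

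**What the plan says.** The Introduction keeps two things apart. One is "muscle atrophy in the paralyzed limbs of patients with hemiplegia", which belongs to the stroke. The other is ICU-acquired weakness, introduced with "In addition to stroke-related disability, critically ill patients may experience other complications" and described as "characterized by generalized weakness of the limbs and respiratory muscles".

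Section 2.7 lists the secondary outcomes, among them the MRC score and grip strength, and then states their purpose: "We aim to investigate these items and quantify ICU-acquired weakness from multiple perspectives".

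Table 2 describes the MRC score. "It evaluates six muscle groups bilaterally", each graded from 0 to 5, with a total from 0 to 60. It adds that "A score below 48 typically indicates clinically significant muscle weakness".

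Table 1 marks MRC and handgrip at day 7 and at discharge, not at admission. The baseline list in Section 2.8 contains neither. Section 2.5 restricts the cohort to acute ischemic stroke and intracerebral hemorrhage.

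Section 2.14 plans multivariable linear regression for continuous secondary outcomes. It does not list the covariates of those models and states no analysis that splits the MRC score at 48.

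**The concern.** The protocol says it will measure weakness that comes on top of the stroke. The MRC sum adds both sides of the body in patients many of whom can be expected to be weak on one side because of the stroke. A point lost to paresis and a point lost to acquired weakness count the same, whether the score is modeled as continuous or compared with 48. With no admission value, the deficit already present at the start cannot be removed by looking at change.

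The likely bias has a direction. MQS combines mobilization level and duration (Section 2.13), and the rehabilitation levels in Section 2.11 rise from passive movement to walking. A patient with dense paresis will plausibly reach lower levels, so have a lower MQS, and will also have a lower MRC sum. Higher MQS would then go with a higher MRC sum even if rehabilitation prevented no acquired weakness. A reader of the results would take that association as support for early dose preventing ICU-acquired weakness, and the data could not bear that reading.

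**Working it through.** **Inputs.** From Table 2: six muscle groups, two sides, grades 0 to 5, reference value 48. From Table 1: MRC at day 7 and discharge only. The grade patterns below are illustrations; the protocol gives no distribution of paresis severity.

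**Step 1: reproduce the stated range.** 6 groups × 2 sides × 5 = 60. This agrees with Table 2.

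**Step 2: one-sided paresis, other side normal.** The normal side gives 6 × 5 = 30. With uniform grade g on the paretic side, total = 30 + 6g.

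| Paretic grade g | Total | Below 48? |
|---|---|---|
| 0 | 30 | yes |
| 1 | 36 | yes |
| 2 | 42 | yes |
| 3 | 48 | no |
| 4 | 54 | no |
| 5 | 60 | no |

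The condition 30 + 6g < 48 gives g < 18/6 = 3. A mean paretic grade below 3 is therefore enough, with no acquired weakness at all. Milder paresis is not.

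**Step 3: one limb only.** The six groups in Table 2 are three in the arm and three in the leg. With arm grade a and leg grade l on the paretic side, total = 30 + 3a + 3l. Complete paralysis of the arm with a normal leg gives 30 + 0 + 15 = 45, and the reverse also gives 45. Both are below 48.

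**Step 4: can the sum tell the two conditions apart?** With uniform grade u on the other side, total = 6u + 6g.

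- Pure stroke deficit, u = 5 and g = 3: 30 + 18 = 48.
- Pure generalized weakness, u = 4 and g = 4: 24 + 24 = 48.
- Stroke deficit only, u = 5 and g = 2: 30 + 12 = 42.
- Milder paresis plus weakness of the other side, u = 4 and g = 3: 24 + 18 = 42.

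Each pair has the same total and a different cause. The non-paretic side alone does distinguish them: 30 against 24 in both pairs.

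**Step 5: relative weight on the continuous scale.** Complete hemiplegia costs 60 − 30 = 30 points. Generalized loss of one full grade everywhere costs 12 × 1 = 12 points. A linear model of the sum can therefore be driven largely by paresis, without any use of the cut-off.

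**Step 6: is the stroke deficit controlled elsewhere?** The National Institutes of Health Stroke Scale (NIHSS) is recorded at admission, day 7 and discharge (Section 2.8), and its baseline value is in the primary model (Section 2.14). Table 2 shows that it includes extremity strength, but also consciousness, visual fields, language, speech and hemi-inattention. Two patients with the same total can differ widely in limb paresis. Adjusting for the total, if the secondary models do so, removes part of the problem only.

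**The case against.** The strongest case against is that the protocol never commits to the reading criticized here. The value 48 stands in a descriptive table as a general marker of muscle weakness; it is not labeled ICU-acquired weakness there, and no analysis classifies patients by it. ICU-acquired weakness is named in one sentence of Section 2.7, to be approached through several items together. The secondary hypotheses in the Introduction concern rectus femoris atrophy and physical performance, and neither needs the MRC score to isolate acquired weakness. As a measure of overall strength after stroke, the bilateral sum is legitimate. NIHSS adjustment would also take up some of the stroke deficit.

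Most of this stands, and it limits the point. A reader might infer that the protocol will diagnose ICU-acquired weakness at 48, or that any hemiparesis falls below it. The documents support neither: no such classification is stated, and uniform grades 3 and 4 with a normal other side score 48 and 54. A reader might also infer that the score measures only the stroke. It does not, because acquired weakness on the non-paretic side still lowers the total.

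What the objection does not remove is the stated purpose in Section 2.7 set against a score that cannot serve it alone. Using several items does not help where an item shares the fault, and linear regression on the sum carries the mixture into the estimate. Which hand is used for grip, and which side for ultrasound, are details an article may leave to the full protocol; they are not counted as errors here.

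**Conclusion.** The point holds as one of interpretation of a secondary outcome. The bilateral MRC sum, with no admission value, mixes hemiparesis with ICU-acquired weakness. An MQS–MRC association cannot be read as an effect on the latter.

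The size that can be shown is on the scale itself: a mean paretic grade below 3 is enough to bring the total under 48, and different causes give identical totals at 48 and at 42. How many patients would be affected cannot be computed, because the protocol gives no distribution of paresis severity.

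Two assumptions carry the conclusion. The illustrations take the non-paretic side to be free of stroke deficit. The direction of bias rests on paresis limiting the mobilization level reached, which is plausible from Sections 2.11 and 2.13 but not stated. The primary outcome, the primary analysis and the sample size are not touched.

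**What to change.** In Section 2.7 and Table 2, state that for the acquired-weakness interpretation the outcome is the MRC score of the non-paretic side, six groups, 0 to 30, analyzed as continuous. Add grip of the non-paretic hand where it is recorded. Report the paretic side and the bilateral sum separately, as overall post-stroke strength. State that a bilateral sum below 48 will not be interpreted as ICU-acquired weakness in this cohort. Do not carry the cut-off over to the half score by scaling, since nothing in the protocol supports a threshold there. State how patients with bilateral paresis, and those with none, are scored.

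The cost is wording. The MRC groups are already graded on both sides, so no new assessment is needed, and enrollment is not scheduled to begin until June 2026. The price is a narrower score range, 0 to 30 instead of 0 to 60, and an explicit rule for patients who have no clear non-paretic side.
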